**Trainees**	
Acceptability and feasibility	How would you describe your experience of completing this training program? How do you value the PFA in your clinical practice? Any indicative changes in behaviors? How would you describe your experience of supporting your patients or colleagues through providing them PFA skills?
Satisfaction	How satisfied are you overall with training module? How clear do you find the concepts and ideas in the module?
Suggestions for further improvement	What do you think could be improved about? Is there anything missing?
Barriers	Are there any difficulties to taking part? What are the barriers to completing training course, and applying training to practice? What are the challenges to complete the assessment, with questions relating to reasons for not taking part/ discontinuation or dropping out?
Process of change	Are there any changes in your perspective of coping acute distress? If the answer is “Yes”, what are they?
**Trainers**	
Acceptability and feasibility	What they thought about the training, what worked, what didn't work?
Satisfaction	How satisfied are you overall with the training session adaptation and development? How well do you find the concepts and ideas organized in the module?
Suggestions for further improvement	What do you least like about the program? What do you think could be improved about? Is there anything missing?
Barriers and facilitators	Are there any difficulties to deliver the training? What are the barriers to deliver training course? What are the challenges to improve training refinement?
**Clinical ward managers**	
Acceptability and feasibility	What is your perspective on the value of psychological first aid for supporting your staff's work? Can you talk about your experience of supporting your staff to participate this training?
Satisfaction	How satisfied of your staff's practice after training completion?
Suggestions for further improvement	What do you least like about the program? What do you think could be improved about? Is there anything missing?
Barriers and facilitators	Are there any difficulties to make them participate the training and practice PFA on frontline? What kind of support would need to enable your team's participation in this training opportunity?
Process of change	Are there any changes in your perspective of your staff to responding to acute distress? What important aspects of diversity you feel when you take a view on this psychological first aid in clinical practice?

##### Observations of Training Sessions

The PFA training adaptation the training sessions will be recorded so the researcher can observe the sessions afterwards. Researchers will make fieldnotes about the delivery of and response to the sessions provided on the program, barriers of training completion, and trainers of task engagement and on its overall structure, delivery, and content of the training (see Table 4). Also, the fidelity of the adapted Chinese PFA training programme will be evaluated. Fidelity checklists will be created for each of module session types to measure how closely they adhere to the RAPID PFA model manual and the intended aims of the interventions based on the domains provided by the Health Behavior Change Competency Framework (HBCC) (77). All training and supervision sessions will be video-recorded and watched by the researcher to rate against the fidelity checklists to ensure training and supervision are delivered as intended (see Table 5). Field notes completed by the trainers during the supervision will also be documented to evaluate whether the participants follow the actions of PFA which may be relevant to the study analysis.

**Table 4 T4:** Observation checklist of PFA training delivery.

To what standard are the core content being delivered?
Are the standard manual and resources being used?
To what extent are the key learning outcomes of each session achieved?
Rate the facilitator 1) Variety of approach to each session using facilitation, presentation, coaching, activities 2) Engagement/rapport with group 3) Group management/involvement 4) Challenge negative behavior within group 5) Positively addressed resistance to program
Additional comments:

**Table 5 T5:** Fidelity checklist of PFA training delivery.

**Domain**	**Assessment method**	**Quality criteria**
Training intervention design	• Assess whether PFA training manual reflect the underlying theoretical model	Prior to study implementation, investigators, and optimally a protocol advisory, should review PFA training manual to ensure that the active ingredients of the RAPID PFA model are fully operationalized. The degree to which the measures reflect the hypothesized theoretical constructs and mechanisms of action should be assessed.
Trainers	• Assess trainers' skills acquisition	Ensure trainers are trained to a well-defined performance Trainers' role-plays should be evaluated for both adherence to PFA components and adherence to process (e.g., interactional style)
Receipt of all PFA training sessions	• Assess degree to what extent of participants understood intervention • Assess participants ability to perform the skills	Verify the participants' understanding of the PFA training information provided Verify that they can use the skills and recommendations discussed (via pre–post-tests, recordings).

### Data Monitoring

Data quality is ensured through several mechanisms, including referential data rules, valid values, range checks, and consistency checks. Checks are applied at the time of data entry into a specific field and monitored by a central data safety and monitoring group.

### Adverse Events Reporting and Harms

The main risk factor is psychological distress among trainees during the training sessions simulation or practice. A contingency plan regarding the use of videotaped testimonials and provision of a stand-by counselor to provide immediate care to the trainees when required has already developed which is explained in the participant information sheet. All changes resulting from adverse events or serious adverse events will be documented. Any participants who become distressed or require additional support during the study's training will stop the training and the person will be invited to a private room and provide a leaflet with information about appropriate sources of support they can access. The trainer who can provide on-site counseling will be able to respond to their needs. If the participant needs a further referral, e.g., medication, or treatment, the researcher will help to receive mental health care and contact.

### Ethical and Dissemination

This trial has been approved by the Institution Review Board from Central South University (XTXL20200610) and by the Psychiatry, Nursing and Midwifery Research Ethics Committee at King's College London, England (LRS/DP-21/22-23161). It also has been processing registration at the Chinese Clinical Trial Registry. Also, this project has been supervised by the PhD researcher's supervisors who are experienced in mental health research. All participants will be asked to provide their written and informed consent acknowledged that all identifying information will be removed.

Several key deliverable and knowledge dissemination strategies will be employed. Findings will be summarized to submit to open-access journals and results will be shared broadly with the policy, practice and academic communities via conference attending and seminars. The use of digital and social medic will be adopted to disseminates project updates and results, as well as generate brief, professionally produced infographics and summaries for dissemination.

## Discussion

Prioritizing the mental health and well-being of healthcare workers is considered an urgent global public health priority (6). Training in PFA has been considered effective to support public mental health in emergencies through reducing acute distress and improving self-efficacy, public health authorities disseminate the training across the globe with the expectation to enhance population level of mental health preparedness and resilience in emergencies. However, a flexible delivery with a neglect for evaluating PFA training has resulted in unintended potential harms, and further prevent generating large effects, which may hamper future proactive uptake and achieve a large level of preparedness, especially for the frontline healthcare workforce. Before establishing what extend potential benefits of PFA training can be contributed to the healthcare context, it has been neglected that determining the feasibility of the PFA training through adapting to the local culture, tailoring to frontline healthcare context, and evaluating systematically is crucial. Considering the COVID-19 pandemic is likely accelerate the uptake of PFA training, it is far more urgent to determine the feasibility of a well-adapted PFA training intervention thereby to effectively inform a RCT in a larger sample. Thus, this study protocol presents a randomized controlled feasibility trial protocol to determine the feasibility and acceptability of a well-adapted PFA training programme for Chinese frontline healthcare workers to improve their ability to provide early emotional support to those in need and self-care, especially in relation to responding to public health emergency situations.

This study has several strengths. First, to our knowledge, this is the first rigorous evaluation of a systematically adapted PFA training intervention for use by frontline healthcare workers which could help to decide the larger follow-on studies of this low-intensity capacity-building programme. Second, as a feasibility-controlled trial combined with a process evaluation, the combination of data regarding retention rate, the ability of the training program to lead to changes in the secondary objectives of interest (i.e., increased preparedness and self-efficacy, reduced burn-out, and secondary traumatic stress, etc.) gained will shape the design and inform a sample size calculation for a future trial. Experience from the training practice will generate a rich and comprehensive understanding of how PFA training might be delivered in the context of a frontline health service and so potentially widen its application to Chinese population. Third, considering that the sample setting has the combing role of emergency response and regular health service in frontline healthcare context, it may contribute to enhance the understanding of its relevance and applicability of findings in different regions, especially in non-disaster frontline settings. Given the overall aim of developing preventive strategies to improve mental health crisis preparedness for frontline healthcare workers, it is consistent with objectives of addressing frontline challenge in public mental health during complex emergencies (81).

## Limitations

There are some limitations of this project. First, the design and evaluation of the feasibility trial has predominately focused on the outcomes associated with the frontline healthcare workers rather than the outcomes for recipients of PFA following a disaster, public health emergency, or other crisis. Second, the timeframe for follow up outcome measures is only 3 months, which may be insufficient time for PFA trainees to apply their knowledge and skills in practice evaluation.

## Conclusions

Psychological First Aid training has been widely proposed as a mental health prevention approach of providing early support to acutely distressed individuals and improving self-efficacy of frontline healthcare workers in responding to crisis, yet it has not been fully evaluated which result in significant flaws of its implementation. This study protocol is designed to evaluate the feasibility and acceptability of a well-adapted PFA training intervention (Preparing Me) for future effectiveness assessment. If it could achieve an 80% retention rate in the end, a main RCT of this educational intervention will be decided, expecting the overall aim of promoting their capacity of recognizing and managing stress when confronted with healthcare emergencies, with an expectation to boost evaluation effort to improve this prevention training approach to achieve a population preparedness. It is anticipated that the resulted information would be an impetus to maximize usability and acceptance of this low-intensity PFA skillset by the wider frontline population, thus achieving the empowerment of the frontline healthcare workforce in dealing with crises at a population level in future emergencies.

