**Method:**

This is a two-armed feasibility randomized controlled trial (RCT) to be conducted among 80 Chinese frontline healthcare workers without prior related mental health training. Participants from the intervention group will receive an adapted PFA training program tailored to the Chinese frontline context to improve their knowledge and skills to support people in crisis. The primary objectives are to evaluate the training intervention's feasibility and the target population's acceptance of this educational intervention. The secondary objective is to obtain preliminary estimates of variability in participants' outcomes over a 3-months period. Measurements are taken pre-intervention (T0), post-intervention (T1), and at 1- and 3-months follow-up (T2–T3). A process evaluation using qualitative research with a subgroup of trainees, their clinical managers as well as trainers will be conducted to gain a comprehensive understanding of the intervention's acceptability and feasibility.

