#### Sample Size

A sample size of between 24 and 50 is considered reasonable in a feasibility study, to be able to estimate a participation rate in anticipation of a full trial (57, 58). Informed by this, the target recruitment for this feasibility trial will be *N* = 80, allowing for a 20% loss to follow-up rate and for at least 64 participants to complete the study during the COVID-19. The sample size is projected to provide enough numbers to be able to estimate the likely efficacy and acceptability of the training intervention to inform the design of a future RCT.

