#### Randomization

The randomization will be performed by an independent researcher not connected with either participant recruitment or data collection, using a 1:1 ratio as per a computer-generated randomization schedule using randomly permuted block sizes by randomization.com. All eligible participants who give written informed consent will be randomly allocated to either the intervention or control arm of the trial. Due to the nature of the study, only the researcher collecting/analyzing the data from trial participants can be masked to the randomization.

As a check on blindness, the researcher will be asked to guess the group allocation of trial participants after they have completed each final follow-up assessment. Unmasking will not occur until databases are closed and the main analysis has been completed.

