### Statistical Data Analysis

Since this is a feasibility study and is not testing hypotheses regarding effectiveness of PFA training intervention, inferential statistics will not be employed. The primary objectives will be addressed via generating estimates of dispersion and central tendency (i.e., proportions, means, SDs, etc.). The acceptable levels of eligibility and enrolment will be a 90% or greater screening eligibility rate for frontline healthcare workers referred to the study. A recruitment rate is expected of 15 trainees per week and the target sample size would therefore be achieved in 6 weeks. The acceptable proportion of enrolled trainees who complete all the training sessions will be 80% or greater, given that there's 18% dropout rate of participants in PFA training cluster RCT (23). The feasibility of collecting quantitative outcome data includes (1) <20% missing data at the group level for each time point and (2) generating estimates of effect and variability related to by the independent research facilitator. Quantitative secondary objectives will be addressed via generating bivariate correlations and regression coefficients for the selected measures. Correlations between the baseline and follow-up will be estimated for continuous outcomes. Measures will be examined for multi-collinearity, as well as any needed transformation due to unfavorable skewness and kurtosis (72, 73). Appropriate 95% confidence intervals will be reported, with differences deemed significant at the 5% level.

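### The only stated progression rule rests on 80% retention and does not refer to the acceptable levels the protocol sets for eligibility, training completion and missing data

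*Protocol article*

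**What the plan says.** The Conclusions state the rule for moving to a main trial: "If it could achieve an 80% retention rate in the end, a main RCT of this educational intervention will be decided". No other section gives a progression rule.

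Statistical Data Analysis sets levels for several feasibility measures:

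- Eligibility: "a 90% or greater screening eligibility rate for frontline healthcare workers referred to the study".
- Training completion: "The acceptable proportion of enrolled trainees who complete all the training sessions will be 80% or greater".
- Missing data: "<20% missing data at the group level for each time point".
- Recruitment: "A recruitment rate is expected of 15 trainees per week". This is worded as an expectation, not as an acceptable level.

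Sample Size plans for N = 80, "allowing for a 20% loss to follow-up rate and for at least 64 participants to complete the study". Randomization allocates "using a 1:1 ratio as per a computer-generated randomization schedule", so about 40 per arm.

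Table 2 and Primary Objectives list loss to follow-up under recruitment and retention. They list missing items or missing questionnaire data separately, under feasibility of the measurement tools.

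**The concern.** The protocol treats recruitment and retention, adherence, and feasibility of the measurement tools as primary feasibility domains, and sets levels for them. The progression rule uses retention only. A participant can stay in follow-up and return questionnaires without having attended every session, so good retention does not imply good training completion. It says nothing about eligibility either. The study could therefore report a go while a level it calls acceptable has not been reached, with no stated consequence.

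The retention level also equals the loss planned for in Sample Size and sits next to a strict limit of below 20% missing. If loss counts as missing, the same result can pass one criterion and fail the other. Unless this is settled before results are seen, the choice of which criterion governs will be made after the fact.

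**Working it through.** **Inputs.** N = 80, 20% loss and 64 completers (Sample Size); 1:1 allocation, taken as 40 per arm (Randomization); 80% retention (Conclusions); below 20% missing, 80% completion and 90% eligibility (Statistical Data Analysis). True retention rates and usable-form rates below are assumptions, shown as ranges. Participants are treated as independent with the same retention in both arms.

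**1. The plan's own figure.** 64 / (1 − 0.20) = 80. It reproduces exactly.

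**2. What the go rule uses.**

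| Measure | Level stated | Named in the go rule? |
|---|---|---|
| Retention | 80% | Yes |
| Screening eligibility | ≥ 90% | No |
| Completion of all sessions | ≥ 80% | No |
| Missing data, each time point | < 20% | No |
| Recruitment | 15 per week, expected | No |

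As an illustration, 64/80 retained with 24/40 PFA trainees (60%) completing all sessions meets the rule as written.

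**3. The boundary, if loss counts as missing.** Missing share = (80 − retained) / 80.

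| Retained | Retention | Missing | Go rule | < 20% missing |
|---|---|---|---|---|
| 63 | 78.75% | 21.25% | fails | fails |
| 64 | 80.0% | 20.0% | met | fails |
| 65 | 81.25% | 18.75% | met | met |

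Pooled over arms, the two criteria disagree at one value only.

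**4. How likely that is.** With X ~ Binomial(80, p):

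| True retention p | P(X ≥ 64), go | P(X ≥ 65) | P(X = 64), clash |
|---|---|---|---|
| 0.75 | 0.18 | 0.12 | 0.06 |
| 0.80 | 0.57 | 0.46 | 0.11 |
| 0.85 | 0.92 | 0.86 | 0.05 |

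Only the last column measures the pooled clash.

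**5. If the group level means each arm, and loss counts as missing.** 32/40 leaves 8/40 = 20.0% missing and fails; 33/40 leaves 7/40 = 17.5% and passes. At p = 0.80, P(X ≥ 33 of 40) = 0.437, so both arms pass with probability 0.437² = 0.19. A go with at least one arm at 20% or more missing has probability 0.38 at p = 0.80 and 0.34 at p = 0.85. A split of 36/40 and 28/40 (90% and 70%) totals 64 and meets the go rule.

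**6. If some retained participants return unusable forms.** Missing = 1 − 0.80 × c, where c is the usable share. For c = 0.98, 0.95 and 0.90 this gives 21.6%, 24% and 28%. To stay below 20%, retention must exceed 0.80 / c, that is 81.6%, 84.2% and 88.9%.

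**7. Precision.** The 95% Wilson interval for 64/80 is 70.0% to 87.3%.

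**8. Effect of adding one criterion.** With 40 PFA trainees and a true completion rate of 80%, P(X ≥ 32 of 40) = 0.59. If completion is independent of retention, P(both met) = 0.57 × 0.59 = 0.34, against 0.57 for retention alone.

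**The case against.** The strongest counter-argument is that the threshold clash depends on a definition the protocol does not give. Table 2 and Primary Objectives keep loss to follow-up apart from missing items and questionnaire data. On that split, 64/80 breaks nothing. Table 2 also lists completion rate beside missing items, so the text is not decisive, but the item-level reading is at least as natural. This stands, and it makes the clash conditional. Even when loss is counted, the pooled clash is one participant wide.

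A reader might infer that the protocol contradicts itself outright, or that the other levels will be disregarded. The documents do not support either. The sentence in the Conclusions does not say that retention decides regardless of other results, and the Discussion expects several kinds of data to shape the future trial. What is shown is an incomplete rule.

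Three further inferences also go too far:

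- That sampling error is ignored: Statistical Data Analysis promises 95% confidence intervals.
- That 15 recruits per week is a pass mark: it is an expectation.
- That deciding on the main trial is the study's only purpose: Objectives and Design also name outcome data collection and estimates of variability.

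Finally, this is a condensed article, and a fuller protocol may set out progression criteria. But the article does state a rule, and that rule does not take up the levels the article itself sets.

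**Conclusion.** The point holds in two parts of unequal strength. The firm part is that the only stated progression rule leaves out the levels for eligibility, training completion and missing data, so a go can be declared with any of them failed. This follows from the text and needs no assumption about definitions.

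The conditional part is the boundary. If loss counts as missing data, the planned 64/80 meets the go rule and misses the strict limit, with probability 0.11 at 80% true retention when arms are pooled. The discrepancy is larger per arm (0.38) or with incomplete forms, and absent if only items on returned questionnaires count.

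No estimate is biased by this. It is a wording defect in a decision rule, worth correcting before results are seen, and not a flaw that invalidates the study.

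**What to change.** - Restate the rule in the Conclusions so that the decision uses 3-month retention together with the acceptable levels in Statistical Data Analysis, with the recruitment rate as a guide.
- State the consequence when a level is missed, for example that the design is amended before a main trial proceeds.
- Define missing data as items or scales missing among returned questionnaires, so that loss is judged once, under retention.
- Say whether the group level means overall or each arm.
- Report retention overall and by arm, with the 95% confidence intervals already promised.

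This changes wording only and needs no extra data. The real cost is that an unconditional go becomes clearly harder to reach: about 0.34 against 0.57 for retention plus training completion under the assumptions in step 8 of the working, and lower again once eligibility and missing data are added. That is a reason to provide an amend-and-proceed outcome rather than a bare pass or fail.
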